**Figure 2 figure2:**
[figure not shown]
Screenshots of the Shining Star study welcome page and table of contents.

### Procedures

An overview of enrollment, intervention, and assessments is provided in Figure 3. Harms and adverse events will be assessed at each visit. Study assessments are low-risk; thus, we anticipate few study-related harms. As this study is ongoing, assessments are described in the present tense.

**Figure 3 figure3:**
[figure not shown]
Schedule of enrollment, intervention, and assessments during study. Feasibility and acceptability will be assessed weekly through the mobile app, and control participants are given access to the intervention after completing all week 12 measures, including 14-day accelerometry. M-PAC: multiple process action control; NIH: National Institutes of Health.

#### Screening

Interested parents complete a web screening tool using a secure online platform [32], which includes information on the preschooler’s age and sex, language fluency, and interest and ability to download the app. Potential participants who met screening criteria are contacted for a phone call, during which a trained staff member inquires about the ability to travel to visits, the preschooler’s ability to wear a device on their wrist, and the preschooler’s habitual PA, sedentary screen time, and sleep. Eligible families are then scheduled for their baseline visit (week 0).

#### Baseline Visit (Week 0)

At this visit (approximately 60-90 min), the study is described in a child-friendly manner to the preschooler, and the parent provides written informed consent. After consent is obtained, preschooler’s height and weight are measured. The preschooler completes developmental tests with a trained researcher, and the parent completes questionnaires. Finally, an accelerometer is secured to the preschooler’s wrist to wear for 2 weeks. The parent is instructed to return the accelerometer, an activity or sleep log, and a home inventory of equipment related to 24-hour movement behaviors after 2 weeks. At the end of the visit, the family is randomized.

If randomized to the intervention, the *Shining Star* mobile app is downloaded onto the parent’s phone. A trained staff member provides a tutorial to explain the mobile app use and set mobile app reminders. The parent’s first weekly lesson and app features are available that day.

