**Night**					
	Week 1: all behaviors—24-h movement to improve sleep	007063: Information on health consequences 007068: Salience of consequences 007024: Self-monitoring of behavior	Knowledge Attitude toward health behavior Perceived susceptibility Behavioral regulation	Instrumental attitude Behavioral regulation	ST^b^ knowledge PA^c^ views Sleep knowledge Social stigma Sleep promoting items in room TV in bedroom Screen availability Sleep parenting practices Portable play items Outdoors Big space or house
	Week 2: sleep—bedtime routines (who, what, and when)	007065: Inform about emotional consequences BCT 007058: Instruction on how to perform the behavior 007055: Demonstration of the behavior	Knowledge Skill Capabilities	Affective judgment Perceived capability	Sleep knowledge Sleep promoting practices ST knowledge ST parenting practices
	Week 3: sleep—how to make the new bedtime routine, routine	007096: Context specific repetition of behavior 007094: Practice behavior 007080: Prompt intended action	Behavioral cuing (problem solving)	Habit formation Behavioral regulation	Scheduling time, chaos Sleep promoting practices
	Week 4: sleep or screen time—bedroom environment	050348 Restructuring the physical environment 050331: Remove averse stimulus 007156: Add objects to the environment 007080 Prompts and cues	Environmental context and resources Behavioral cuing	Perceived opportunity Affective judgment Habit	Television in bedroom Sleep promoting items in room Bed or room sharing Screen availability
	Week 5: sleep— parent sleep habits	007063: Information on health consequences 007068: Salience of consequences 007057: Draw attention to incompatible beliefs 007159 Affirm valued self-identity	Knowledge Attitude toward health behavior Perceived susceptibility	Instrumental attitude Identity	Sleep knowledge Sleep views
	Week 6: sleep—how family members can support goals	050346: Directly restructure the social environment BCT 007030: Advise to seek instrumental support 0007257: Provide positive material consequence for behavior	Social context and resources Behavioral cuing Social influences Reinforcement	Perceived opportunity Identity Behavioral regulation Affective judgment	Sleep promoting practices Bed or room sharing ST parenting practices Screen availability Childcare arrangement Family structure

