### Measures

#### Primary Outcome

Our primary outcome is adherence to all 3 of the 24-hour Movement Guidelines. Preschoolers’ PA and sleep were assessed in 15-second epochs using the Actigraph GT3X+ accelerometer. Preschoolers wear this device on their wrist using a Velcro band, only removing it for water-based activities (eg, bath). Accelerometer data will be evaluated using the Sadeh algorithm to detect sleep periods and compared with the parent-report of sleep [33]. Periods of ≥20 minutes of continuous zeroes during the day will be removed as nonwear time [34,35]. Validated cut points for wrist measurement in this age range will be used for sedentary behavior (0-328 counts per 5 seconds), light PA (329-1392 counts per 5 seconds), and MVPA (≥1393 counts per 5 seconds) [36]. Total PA is the sum of light PA and MVPA. Preschoolers with ≥3 days (at least 1 weekday and 1 weekend day) of ≥10 hours of wear, and 3 days of sleep, will be included for analysis, similar to another wrist-worn protocol [37], and is the estimated minimum for accelerometer wear in this age range [38,39]. To capture adherence to the sedentary screen time guideline, parents are asked, “On an average 24-hour period, how much time does your child spend using electronic screen devices (such as a smartphone, tablet, video game, or watch television or movies, videos on the internet) while they are sitting or lying down?” with a free response option. This question is conducted at screening and subsequent visits and was chosen to align with surveillance efforts of movement behaviors [40]. This questionnaire reflects the previous week before accelerometer wear. The sum of guidelines obtained based on these measures, and if the participant meets all 3 guidelines, will be used for analysis.

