#### Exploratory Aims

We will also conduct an intent-to-treat analysis using a log-binomial regression or Poisson with robust variance to adjust for baseline recommendation number and randomization strata (age and sex). Linear regression will also be used to compare changes in exploratory outcomes between treatment and control groups with adjustment for baseline values. If demographic differences, such as income, are found between the 2 groups, we will conduct a sensitivity analysis with these variables for adjustment. These exploratory outcomes include, in priority order: number of recommendations obtained (range: 0-3), individual 24-hour movement behaviors, anthropometry, early child motor battery scores, early child cognitive battery scores, executive functioning scores, and behavioral problem scores. Descriptive characteristics will also be explored, such as PA and accessibility score, household chaos score, parental support of PA, parental perceived influence on screen time, family regularity index, child preferences for PA, and theoretical component changes (eg, intention and behavioral support for PA). We will also explore the ideal change in behaviors using isotemporal substitution analysis, whereby evaluating substitution of one behavior (eg, sedentary behavior) for another (eg, MVPA) with change in child developmental outcomes.

Furthermore, we will examine the relationship between meeting specific recommendations and child outcomes, with a mediator of theoretical component changes (eg, habit formation scores). Mediation analysis will be conducted using the PROCESS vs 3.5 macro with 10,000 bootstrap intervals with unstandardized estimates and CIs [63]. These exploratory outcome testing will be subject to the Benjamini-Hochberg adjustment for multiple comparisons [64].

As for missing data, we will describe differences in baseline characteristics between participants with complete versus incomplete follow-up. Sensitivity analyses based on multiple imputation methods will be conducted to examine the robustness of our findings with respect to missing data.

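### The device-measured baseline for physical activity and sleep is recorded after randomization with the app already open in one arm, so it should not serve as baseline in the exploratory adjusted models

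*Protocol article*

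**What the plan says.** The order of events is set out in the protocol article under Baseline Visit (Week 0). Consent, height and weight, developmental tests and parent questionnaires come first. An accelerometer is then put on the child's "wrist to wear for 2 weeks", and the device, a log and a home equipment inventory are to be returned after those two weeks. "At the end of the visit, the family is randomized". For intervention families the app is installed at once, and the "first weekly lesson and app features are available that day". No run-in wear period and no delay in app access is described.

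Table 1 shows what falls in the two-week window. The week 1 lesson covers all behaviors ("24-h movement to improve sleep") and includes self-monitoring. The week 2 lesson is on "bedtime routines (who, what, and when").

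Under Primary Outcome, physical activity and sleep come from the accelerometer and screen time from a parent question. "The sum of guidelines obtained based on these measures", together with all-three status, goes into the analysis. On the screen time question the section adds: "This questionnaire reflects the previous week before accelerometer wear".

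Under Aim 1 the primary analysis is a chi-square comparison of the proportions meeting all three guidelines at 12 weeks. Under Exploratory Aims an intent-to-treat regression is to "adjust for baseline recommendation number and randomization strata (age and sex"). Linear regression then compares change in the exploratory outcomes with adjustment for baseline values. Guideline count and the individual movement behaviors stand first in the priority order.

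**The concern.** A baseline covariate is safe to adjust for because treatment cannot have influenced it. That does not hold for the week 0 accelerometry: almost all of it is recorded after allocation is known and, in the intervention arm, after the app has opened. If the opening lessons do anything in their first two weeks, part of the treatment effect sits in the covariate, and adjusting for it takes that part out of the estimate. A baseline table of device-based guideline status by arm would also compare families already treated with families not treated.

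At stake are the exploratory estimates for device-measured physical activity and sleep, for which this wear is the only device baseline described. Isotemporal and mediation analyses would inherit the problem if they use change from this wear. The home inventory, returned after the same two weeks, is exposed in the same way. The legend to Figure 3 gives controls the app only after the 14-day wear at week 12, so the protocol guards that wear against exposure but not the week 0 wear.

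**Working it through.** **Step 1. Which measures precede randomization?**

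| Measure | Timing | Status as baseline |
|---|---|---|
| Parent report of activity, sleep and screen time | Screening call | Clean |
| Screen time question | Week 0 visit, about the week before wear | Clean |
| Anthropometry, developmental tests, questionnaires | Week 0 visit, before randomization | Clean |
| Accelerometer activity and sleep | Two weeks after the visit | Post-randomization, on treatment in one arm |
| Home inventory | Returned after two weeks | Post-randomization, on treatment in one arm |

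**Step 2. Which analyses use the exposed measures?**

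- Aim 1 chi-square: uses no baseline value, so it is unaffected.
- Baseline-adjusted change models for device activity and sleep: affected.
- Guideline-count and adjusted intent-to-treat models: these depend on what baseline recommendation number means. The protocol does not define it. If it is the screening count, the covariate is clean. If it is the count built as under Primary Outcome, its activity and sleep parts are exposed and its screen time part is not.

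**Step 3. Size of the bias.** Let d be the true 12-week effect, f the fraction of d already present in weeks 0 to 2, and r the within-arm baseline to week 12 correlation (equal to the regression slope when the two variances are equal). The arms then differ by f·d at baseline and by d at week 12.

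- Week 12 value adjusted for baseline: d − r·(f·d) = d·(1 − r·f).
- Change adjusted for baseline: (d − f·d) − (r − 1)·(f·d) = d·(1 − r·f), the same.
- Unadjusted week 12 difference: d.

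The documents give neither f nor r. Under assumed values the share of the effect retained is:

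| f | r = 0.3 | r = 0.5 | r = 0.7 |
|---|---|---|---|
| 0 | 100% | 100% | 100% |
| 0.10 | 97% | 95% | 93% |
| 0.25 | 92.5% | 87.5% | 82.5% |
| 0.50 | 85% | 75% | 65% |

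A simulation with 400,000 subjects per setting agreed. The adjusted model retained 0.875 and 0.828 at f = 0.25, and 0.743 and 0.649 at f = 0.50, for r = 0.5 and 0.7 in that order. The unadjusted week 12 difference retained 0.99 to 1.00. The formula is for linear models. For the log-binomial or Poisson model it indicates direction, not exact size.

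**Step 4. Power.** These figures assume 30 per arm and a true effect of 0.65 SD, which is not a protocol value. They come from repeated simulations, and a range shows the spread between runs.

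| Model | r = 0.5 | r = 0.7 |
|---|---|---|
| Adjusted, true pre-randomization device baseline | 80–81% | 93% |
| Adjusted, week 0 to 2 wear, f = 0.25 | 69% | 80–81% |
| Unadjusted week 12 comparison | about 70% | about 70% |

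The first row cannot be had for families already randomized. The realistic comparison is between the second and third rows, and there dropping the exposed covariate does not reliably gain power.

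**The case against.** The best defence concerns reach and size, since the order of events is explicit.

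- **The primary analysis is untouched.** This stands. A reader might infer that the trial's main test is biased. It is not: Aim 1 and the sample size calculation both rest on 12-week status without any baseline value.
- **Most baselines are clean.** This stands too. Screen time, anthropometry, and motor, cognitive, executive-function and behavior scores are obtained before randomization.
- **Baseline recommendation number may be the screening count.** This is plausible. Eligibility is set on that count, and the parent activity and sleep questions are listed as repeated only at weeks 6 and 12. The text does not settle the matter, so for the intent-to-treat model the point is an ambiguity and not a demonstrated bias. It does not help the models for the individual device-measured behaviors.
- **The effect in two weeks may be small.** This is fair, above all for physical activity, whose lessons run in weeks 9 to 12 and which only the week 1 overview touches in the window. For sleep an early effect is more credible. The trial cannot presume that its own opening lessons are inert.
- **A change score loses the whole fraction f.** A reader might infer this, but it applies only to unadjusted change. The protocol adjusts change for baseline, so the loss is r·f.
- **The fix may not raise power.** This stands, as Step 4 shows. The case for it is bias.

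**Conclusion.** The point holds for the exploratory analyses that use week 0 to 2 accelerometry as a covariate or as the origin of change. On the protocol's own sequence that record is post-randomization, and adjusting for it multiplies the estimated effect by 1 − r·f. Over the assumed ranges 65% to 97% of the effect is retained. The exact figure cannot be known from the documents, and with no effect in the first two weeks there is no bias.

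The documents do not support reading this as a flaw in the primary chi-square, as exposure of every baseline measure, or as a fixed power loss that a change of covariate would recover. It is a cheap improvement to the exploratory analyses. It is worth settling now because 39 of the planned 80 families had been randomized by October 2025, and a pre-randomization device baseline cannot be obtained for them.

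**What to change.** 1. Define baseline recommendation number as the parent-report count from the screening call, and use that in the adjusted intent-to-treat model.
2. Do not use week 0 to 2 accelerometry as a covariate or as the origin of a change score. Report it as an early post-randomization measure, and treat the take-home inventory in the same way.
3. Compare week 12 device-measured activity and sleep directly between arms, adjusted for age, sex and the pre-randomization parent report.
4. Keep the planned baseline adjustment for outcomes measured at the week 0 visit before randomization.
5. For families not yet enrolled, reconcile the order of device wear, randomization and app activation with the use of that wear as baseline.

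Items 1 to 4 change analysis wording only. Item 5 would be procedural if the sequence is altered. The cost is precision: parent report, restricted by eligibility to a count of 0 or 1, predicts week 12 device values less well than a true device baseline would.

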#### Follow-up Visits (Week 6 and Week 12)

At the second visit (approximately 60-90 min; week 6), families return to complete preschooler anthropometrics, preschooler development tests, and parent questionnaires. Procedures are completed similarly to the baseline visit. Preschoolers are fitted with an accelerometer, and parents are asked to return the device, activity or sleep log, and home inventory after 2 weeks of wear. The trained staff answer any questions on the mobile app for families in the intervention group.

At the final visit (approximately 60-90 min; week 12), families return to complete preschooler anthropometrics, preschooler development tests, and parent questionnaires. Procedures are completed similarly to the baseline visit. Preschoolers are fitted with an accelerometer, and parents are asked to return the device, activity or sleep log, and home inventory after 2 weeks of wear. Parents in the intervention are allowed to delete the mobile app or continue viewing the content. Parents randomized to the control are allowed to download the mobile app, receive a tutorial, and access all mobile app lessons and features.

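### The final-visit text and the Figure 3 legend are inconsistent on when wait-list controls get the app; on the visit-day reading, controls are exposed while the activity and sleep components of the primary outcome are measured

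*Protocol article*

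**What the plan says.** Two places in the protocol article deal with control access.

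- **Follow-up Visits (Week 6 and Week 12).** The week-12 paragraph begins: "At the final visit (approximately 60-90 min; week 12), families return to complete preschooler anthropometrics, preschooler development tests, and parent questionnaires". It says procedures run as at baseline, and continues: "Preschoolers are fitted with an accelerometer, and parents are asked to return the device" along with the log and home inventory after two weeks. It then says intervention parents may delete or keep the app, and ends: "Parents randomized to the control are allowed to download the mobile app, receive a tutorial, and access all mobile app lessons and features".
- **Figure 3 legend.** Here the timing is explicit: "control participants are given access to the intervention after completing all week 12 measures, including 14-day accelerometry".

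The Primary Outcome section shows which measurements fall in the wear period. The endpoint is composite: "Our primary outcome is adherence to all 3 of the 24-hour Movement Guidelines". Two components come from the device: "Preschoolers’ PA and sleep were assessed in 15-second epochs using the Actigraph GT3X+ accelerometer". The third, sedentary screen time, is a parent report, of which the article says: "This questionnaire reflects the previous week before accelerometer wear". Aim 1 compares the arms at 12 weeks on the proportion meeting all three, by chi-square.

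**The concern.** The primary comparison is between families who have the app and families who do not yet have it. It is sound only if controls stay without the app until their week-12 measurement is complete, and that measurement does not end at the visit. The device goes on at the visit and records for the next two weeks. If staff give the tutorial and open the lessons at the same visit, the control arm has the whole programme available throughout the period in which its activity and sleep are recorded.

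Any effect of the app over those two weeks would raise the control rate and shrink the difference. Exposure during outcome measurement cannot be undone later. As of October 2025, 28 families had completed the final visit, so with 80 planned, up to 80 − 28 = 52 final visits were still to come. That makes the wording worth settling now.

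**Working it through.** **1. The two statements side by side**

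| | Figure 3 legend | Final-visit paragraph |
|---|---|---|
| Control access | After all week-12 measures, including the 14-day wear | Listed among the events of the week-12 visit |
| Timing relative to wear | Explicit: after | Not stated |

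Three features make access at the visit the natural reading of the paragraph:

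- It opens by placing its events at the visit.
- It says procedures follow the baseline pattern. At baseline, intervention parents get the download and tutorial at the visit and can use the app the same day, while a two-week wear is starting.
- The tutorial is a staff activity, and the paragraph names no later visit at which it could be given.

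**2. What access at the visit could change**

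| Component | Source | Period | Exposed under the visit-day reading? |
|---|---|---|---|
| Physical activity | Accelerometer | Two weeks after the visit | Yes |
| Sleep | Accelerometer | Two weeks after the visit | Yes |
| Screen time | Parent report | Week before wear | No |

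All three must be met, so in the control arm

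P(all three) ≤ P(screen time met in the week before wear).

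A control child who fails screen time stays a failure whatever happens during wear. Exposure can matter only for controls who already meet screen time.

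**3. The plan's own power figure**

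Inputs from Sample Size and Power Calculation: 30 per arm, 5% versus 35%, significance level .05 (taken as two-sided). Exact power is the sum, over all pairs (a, b) of successes in the two arms, of Bin(a; 30, p_control) × Bin(b; 30, 0.35) wherever the test gives P ≤ .05.

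- Fisher's exact test: 78.8%, close to the stated 80%.
- Uncorrected chi-square: 88.0%. The same method gives 80.8% at 24 per arm, and 63.3% for 5% versus 25% at 30 per arm, against the article's 80% and 63.5%.
- Dropout: 30 / (1 − 0.25) = 40 per arm, as stated.

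**4. Illustration of a raised control rate**

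The raised rate is an assumption; no such figure is in the documents. Intervention rate 35%, 30 per arm:

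| Control rate | Exact, uncorrected chi-square | Fisher |
|---|---|---|
| 5% (plan) | 88.0% | 78.8% |
| 7.5% (assumed) | 77.6% | 66.8% |

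The loss is 88.0 − 77.6 = 10.4 points by chi-square and 78.8 − 66.8 = 12.0 points by Fisher. By step 2, the 7.5% row is possible only if at least 7.5% of controls met screen time before wear.

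**The case against.** The strongest reply is that there is no contradiction. The legend belongs to the figure that sets out the schedule, and it states a clear rule. The visit paragraph gives no competing time: it says what control parents are allowed to do, after the sentences on returning the device, and it does not say access starts that day, as the baseline text does for the intervention arm. Recruitment Plans mentions contact to pick up accelerometers, so there is an occasion after wear when the app could be handed over. This stands in part. The two passages can be read together, and the design in the legend is sound. The paragraph that describes the visit should still not depend on a figure legend to prevent a misreading.

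The second reply concerns size, and it stands. A reader might infer that the wear supplies the whole primary outcome and that the control rate could rise to 10% or 15%, with power of 66% or 44% (exact, uncorrected chi-square). The documents do not support that. Screen time is fixed before wear, and it is the guideline the article expects few children to meet. The sample-size section likens the starting point to a study in which 5% met it. If about 5% of controls met screen time, early access could not lift the all-three rate above about 5%.

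A reader might also infer that early access has already occurred, since 28 families have finished. The article does not say what was done at those visits, nor how the 28 divide between arms.

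**Conclusion.** The point holds as an inconsistency of wording with a possible consequence for the primary comparison. It is not a demonstrated design fault. The legend delays control access until the wear is complete; the final-visit paragraph, on its natural reading, does not. If the visit-day reading was followed, or is followed in future, the activity and sleep components in the control arm are measured under exposure, and the likely direction of bias is toward no difference. If the legend was followed, nothing in the comparison or the stated power is affected.

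The size is unknown and is limited by the share of controls already meeting screen time before wear. The fall in power from 88% to 78% is an illustration resting on an assumed control rate of 7.5%, an unchanged 35% in the intervention arm and 30 analysed per arm. It is not an estimate.

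**What to change.** 1. **Reconcile the text.** Make the final-visit paragraph and the Figure 3 legend state one rule for control access, and confirm that site staff follow it before further final visits. The timing in the legend is the one that keeps controls unexposed during measurement.
2. **Check what was done.** For control families already finished, establish when the app was made available and report how many had access during the week-12 wear.
3. **If any did, add a sensitivity analysis** of the primary comparison that addresses those families. One option is to treat their wear-based components as missing within the multiple imputation already planned.

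Leave the primary scoring and the sample size as they are. In particular, do not score controls only on wear days before app access. If access came on the day of fitting, almost no such days exist and those children would fail the three-day minimum. Such a filter would also shorten the measurement window in one arm only, on the basis of an event after randomisation.

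The cost is a wording correction, a small check of records and, at most, one extra analysis.
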